## **2.5 Sample size**

To assess the cumulative incidence after 10 months of follow-up in residential care centers in Belgium a sample of 381 participants (residents & staff) is required to estimate a proportion of 0.5 with a half-width of 5%, using a 95% Wilson score CI. As residents/staff are clustered within care facilities, the sample size will be augmented by the design effect. Assuming, 15 participants (7 residents and 8 staff) per institution after 10 months of follow-up, and an ICC of 0.12, the design effect is  $2.68 = (1 + 0.12 \times (15 - 1))$ . The total sample size required is  $1022 = 381 \times 2.68$ . At least 69 institutions, each including 15 participants, need to be included in this study, which brings the total sample size to 1035 after 10 months follow-up. In order to obtain at least 15 participants, in 69 institutions after 10 months of follow-up, assuming a drop-out rate of 0.2 and 0.4 for staff (changes in staff, sick leave and holidays) and residents (deceased, hospitalized or transferred residents), would require 22 sero-negative participants per care facility, (10 staff, 12 residents) in all 69 institutions. Assuming a seroprevalence rate of 0.5 at the baseline moment of the study would require 44 participants per care facility, (20 staff, 24 residents) in all 69 institutions.

A final sample size calculation will be performed to check whether the sample size obtained for the second research question will be sufficient for the analysis of the first research question.

To assess the seroprevalence in residential care centers in Belgium a sample of 381 participants (residents & staff) is required to estimate a seroprevalence of 0.5 with a half-width of 5%, using a 95% Wilson score CI.

As residents/staff are clustered within care facilities, the sample size will be augmented by the design effect. Based on the previous calculation, 44 participants (24 residents and 20 staff) will be sampled per institution. Assuming an ICC of 0.12, the design effect is  $6.16 = (1 + 0.12 \times (44 - 1))$ . The total sample size required is  $2347 = 381 \times 6.16$ . At least 54 institutions, each including 44 participants, need to be included in this study, which brings the total sample size to 2376 participants.

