### **2.7.2 Demographic and medical data.**

Data to be extracted from the Sciensano database are a list of all nursing homes in Belgium with their RIZIV number, postal code, the capacity of each nursing home (number of beds), and suspected (CT and symptoms) and confirmed (PCR and AG POC test) COVID-19 related death rate.

At the NH level, the management will be asked, at baseline, about the proportion of care grade (according to the Katz evaluation scale) among their residents, if a COVID-19 vaccination campaign was organized in the NH yet (date, type of vaccine and vaccination coverage), the suspected and confirmed COVID-19 infection rate, the COVID-19 related and non-COVID-19 related death rate from the beginning of the crisis until now and if and when they had an outbreak (more than one COVID-19 infection that are suspected to be related). With every follow-up sampling timepoint, the NH will be asked about a vaccination campaign (when this did not take place yet at baseline), if COVID-19 testing was performed in their NH, the respective proportion of positive tests and COVID-19 related death rate.

Individual medical data, comprising medical history and if participants have experienced an episode of COVID-19 symptoms or underwent a COVID-19 (PCR/antigen) test (with mention of date and result) or if COVID-19 was confirmed by a CT-scan, reason of missing data of drop outs (death, hospitalisation, sick leave, leaving the job), and whether they received a COVID-19 vaccination (date, type of vaccine, number of doses) in both NH residents and staff will be collected through an online questionnaire at both baseline and follow-up sampling timepoints (LimeSurvey) (See Appendix 6.3 for questionnaires). The CRC will fill out the questionnaire concerning the resident participants during the week of the sampling timepoint. Therefore the head of the nursing staff or the representative of the resident can be asked to provide the data. In this questionnaire, the surveyed medical data will be linked to the participant identification code. Concerning the medical history, the participants (NH staff and residents) will be asked

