**Versie voor deelnemende medewerkers:**

1. Gelieve uw uniek studienummer in te vullen.
2. Neemt u nog deel aan de studie (zal deze vragenlijst vervolledigd worden) ?  
Zo neen, waarom niet?

*Door de onderzoeker in te vullen*

- a. Tussentijdse afwezigheid in de studie (ziekte, vakantie, hospitalisatie ...)
- b. Deelnemer wenst niet meer deel te nemen
- a. Vermoedelijk of bewezen COVID-19 overlijden                      datum van overlijden:
- b. Niet-COVID-19 gerelateerd overlijden                      datum van overlijden:
- c. Medewerker is niet langer werkzaam in het WZC

*Vraag 3 wordt enkel toegevoegd indien voordien neen werd geantwoord.*

3. Bent u gevaccineerd tegen COVID-19?
  - a. Ja, 1 dosis
  - b. Ja, 2 dosissen
  - c. Neen
  - d. Zo ja, welk vaccin kreeg u toegediend
    - i. Het AstraZeneca/Oxford vaccin
    - ii. Het BioNtech-Pfizer vaccin
    - iii. Het Moderna vaccin
    - iv. andere
  - e. Zo ja, datum van vaccinatie (eerste spuit).
4. Bent u in de afgelopen twee maanden getest geweest op het coronavirus (via PCR/ag-sneltest/of radiologisch via CT-scan)? Ja/Nee
5. Zo ja. Bent u in de afgelopen 2 maanden (tussen de vorige testronde en nu) positief getest?  
*Meerdere antwoordmogelijkheden*
  - Ja, via PCR-test (test waarbij men via een neuswisser een staal afneemt en u na labo-analyse het resultaat krijgt)
  - Ja, via antigeen sneltest (test waarbij men via een neuswisser een staal afneemt en men binnen het kwartier het resultaat kan aflezen)
  - Ja radiologisch, via een CT-scan
  - neen
6. Zo ja, datum van 1ste positieve PCR-test of sneltest in de afgelopen 2 maanden (bij benadering)?

7. Indien COVID-19 radiologisch bevestigd werd via een CT-scan , vermeld de datum van deze CT-scan.
8. Hebt u in de afgelopen 2 maand (tussen de vorige testronde en nu) een periode 1 of meerdere van volgende symptomen ervaren, zonder dat hier een duidelijke verklaring voor was? Duid aan wat van toepassing is (meerdere antwoordmogelijkheden).
  - Hoest
  - Kortademigheid
  - Pijn op de borst
  - Smaakverlies
  - Geurverlies
  - Verergering van chronische respiratoire aandoeningen (vb. COPD, astma, chronische hoest,...)
  - Koorts
  - Spierpijn
  - Vermoeidheid
  - Loopneus/verstopte neus
  - Keelpijn
  - Hoofdpijn
  - Verlies van eetlust
  - Diarree
  - Acute verwardheid
  - Plotse val
9. Zo ja, wanneer hebt u, bij benadering, deze symptomen ervaren? Gelieve de dag aan te geven waarop deze symptomen zijn begonnen.

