### **Versie voor deelnemende bewoners**

*(in te vullen door de onderzoeker; bevragen bij de (hoofd)verpleegkundige of de vertegenwoordiger van de bewoner):*

1. Gelieve het uniek studie nummer van de deelnemer in te vullen.
2. Neemt de bewoner nog deel aan de studie (zal deze vragenlijst vervolledigd worden)?  
ja/neen  
Zo neen, waarom niet?
  - a. Vermoedelijk of bewezen COVID-overlijden (datum overlijden)
  - b. Niet-COVID-19 gerelateerd overlijden (datum overlijden)
  - c. Bewoner wenst niet meer deel te nemen

*Vraag 3 wordt enkel toegevoegd indien voordien neen werd geantwoord.*

3. Is bewoner gevaccineerd tegen COVID-19?
  - a. Ja, 1 dosis
  - b. Ja, 2 dosissen
  - c. Neen
  - d. Zo ja, welk vaccin werd toegediend
    - i. Het AstraZeneca/Oxford vaccin
    - ii. Het BioNtech-Pfizer vaccin
    - iii. Het Moderna vaccin
    - iv. andere
  - e. Zo ja, datum van vaccinatie (eerste spuit).
- 4.

5. Is de deelnemer in de afgelopen twee maanden getest geweest op het coronavirus (via PCR/ag-sneltest/of radiologisch via CT-scan)? Ja/Nee
6. Zo, ja. Is de deelnemer in de afgelopen 2 maand (tussen de vorige testronde en nu) **positief** getest op het coronavirus?
  - Ja, via PCR-test (test waarbij men via een neuswisser een staal afneemt en u na labo-analyse het resultaat krijgt)
  - Ja, via antigen sneltest (test waarbij men via neuswisser een staal afneemt en men binnen het kwartier het resultaat kan aflezen)
  - Ja, radiologisch, via een CT-scan
  - Neen
7. Zo ja, datum van 1ste positieve PCR-test of sneltest de voorbije 2 maanden (bij benadering)?
8. Indien de COVID-19 radiologisch bevestigd werd via een CT-scan, vermeld de datum waarop dit is gebeurd.
9. Heeft de deelnemer in de afgelopen 2 maand (tussen de vorige testronde en nu) een periode 1 of meerdere van volgende symptomen ervaren, zonder dat hier een duidelijke verklaring voor was? Duid aan wat van toepassing is (meerdere antwoordmogelijkheden).
  - Hoest
  - Kortademigheid
  - Pijn op de borst
  - Smaakverlies
  - Geurverlies
  - Verergering van chronische respiratoire aandoeningen (vb. COPD, astma, chronische hoest,...)
  - Koorts
  - Spierpijn
  - Vermoeidheid
  - Loopneus/verstopte neus
  - Keelpijn
  - Hoofdpijn
  - Verlies van eetlust
  - Diarree
  - Acute verwardheid
  - Plotse val
10. Zo ja, wanneer heeft de deelnemer, bij benadering, deze symptomen ervaren? Gelieve de dag aan te geven waarop deze symptomen zijn begonnen.

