### **Version pour les résidents participants**

(à remplir par l'examineur; à demander par l'infirmière ou l'infirmière en chef ou le représentant du résident):

12. Veuillez saisir le numéro d'étude unique du participant.

13. Le résident participe-t-il toujours à l'étude (ce questionnaire sera-t-il rempli)? Oui Non

Si non, pourquoi pas?

- a. Décès COVID présumé ou prouvé (date du décès)
- b. Décès non lié au COVID-19 (date du décès)
- c. Le résident ne souhaite plus participer

*La question 14 n'est ajoutée que si la réponse était non auparavant.*

14. • Le participant a-t-il été vacciné contre le COVID-19?

o Si oui, quel vaccin le participant a-t-il reçu

- ☐ Le vaccin AstraZeneca / Oxford
- ☐ Le vaccin BioNtech-Pfizer
- ☐ Le vaccin Moderna

o Si oui, date de vaccination (première seringue).

15. Le participant a-t-il été testé pour le coronavirus (via PCR / test rapide ag / ou radiologiquement via CT scan) au cours des deux derniers mois? Oui Non

16. Si c'est le cas. Le participant a-t-il été testé positif pour le coronavirus au cours des 2 derniers mois (entre le cycle de test précédent et maintenant)?

- Oui, via un test PCR (test dans lequel un échantillon est prélevé via un écouvillon nasal et vous obtenez le résultat après analyse en laboratoire)
- Oui, via un test rapide d'antigène (test dans lequel un échantillon est prélevé via un tampon nasal et le résultat peut être lu en 15 minutes)
- Oui, radiologiquement, via un scanner
- Non

17. Si oui, date du 1er test PCR positif ou test rapide au cours des 2 derniers mois (approximative)?

18. Si le COVID-19 a été confirmé radiologiquement par un scanner, indiquez la date à laquelle cela s'est produit.

19. Le participant a-t-il ressenti un ou plusieurs des symptômes suivants au cours des 2 derniers mois (entre le cycle de test précédent et maintenant), sans aucune explication claire à ce sujet? Indiquez ce qui s'applique (options de réponses multiples).

- Toux
- Essoufflement
- Douleur thoracique
- Perte de goût
- Perte d'odeur
- Aggravation des maladies respiratoires chroniques (ex: BPCO, asthme, toux chronique, ...)
- Fièvre
- fatigue musculaire
- Fatigue
- Nez qui coule / bouché
- Gorge irritée
- Mal de crâne
- Perte d'appétit
- La diarrhée
- Confusion aiguë
- Chute soudaine

20. Si oui, quand le participant a-t-il ressenti ces symptômes? Veuillez indiquer le jour où ces symptômes ont commencé.

21. Le cas échéant, le participant a-t-il été vacciné avec un vaccin contre le COVID-19?  

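### The resident follow-up form has no code for hospitalisation, transfer or any other exit besides death and refusal, although the protocol expects these exits and analyses resident mortality

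*Protocol*

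**What the plan says.** Four places in the Protocol bear on this.

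- **Section 2.5** sets the attrition: "assuming a drop-out rate of 0.2 and 0.4 for staff (changes in staff, sick leave and holidays) and residents (deceased, hospitalized or transferred residents". Three reasons are given for residents, and refusal is not one of them.
- **Section 2.7.2** says the online questionnaire will collect, for residents and staff alike, the "reason of missing data of drop outs (death, hospitalisation, sick leave, leaving the job". Hospitalisation is listed and transfer is not.
- **The resident follow-up form (6.3 Appendix 3)** first asks whether the resident still takes part, with a gloss asking whether the questionnaire will be completed. If the answer is no, the Dutch version offers "Vermoedelijk of bewezen COVID-overlijden (datum overlijden", "Niet-COVID-19 gerelateerd overlijden (datum overlijden" and "Bewoner wenst niet meer deel te nemen". These are a dated suspected or proven COVID death, a dated non-COVID death, and an undated wish to stop. The French version has the same three and ends with "Le résident ne souhaite plus participer". Neither has a free-text or other option.
- **The staff follow-up form** adds "Tussentijdse afwezigheid in de studie (ziekte, vakantie, hospitalisatie" (temporary absence for illness, holiday or hospital stay) and "Medewerker is niet langer werkzaam in het WZC" (no longer employed at the home). The French staff form matches.

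Section 3.2, item 6, models time to confirmed COVID-19 death in vaccinated residents, with other death as a competing risk. Item 9 does the same for vaccinated against non-vaccinated residents, if there are enough of the latter.

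**The concern.** Two of the three reasons that Section 2.5 expects for resident drop-out have no code on the form meant to record them. The only code for a living resident is refusal, which Section 2.5 does not list and which carries no date. The staff form has the matching codes, so the gap falls on the group whose mortality is analysed.

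What is at stake is the censoring in the mortality models. A cause-specific Cox model assumes that residents censored at a given time have the same later hazard, given the covariates, as those still followed. Residents who go to hospital or move elsewhere plausibly do not. If they cannot be told apart from refusals, or have no exit date, the analyst can neither place the censoring time properly nor run a sensitivity analysis on that group. An analysis plan cannot repair this later, because a reason or date that was never collected cannot be recovered.

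**Working it through.** **Step 1. Expected exits against available codes.**

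| Reason for exit | Section 2.5 (residents) | Section 2.7.2 | Resident form | Staff form |
|---|---|---|---|---|
| Death | yes | yes | two codes, dated | two codes, dated |
| Hospitalisation or temporary absence | yes | yes | none | yes |
| Transfer or leaving the home | yes | only leaving employment | none | yes (leaving employment) |
| Refusal | no | no | yes, undated | yes |
| Other | no | no | none | none |

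For residents, two rows that the text expects are empty on the form.

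**Step 2. Where else the information could be held.** Section 2.7.3 has the reason for an unperformed test documented and names hospitalisation. That covers a missed test, but it names no transfer and gives no vital status. The nursing-home follow-up questionnaire asks for the number of COVID-19 deaths in the home over two months. Those are totals, not linked to participants, and exclude other deaths. No section says how vital status is obtained once a resident has left the home.

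**Step 3. Reproduce the plan's attrition figures.**
- Retained per home from the seronegative participants: 10 × (1 − 0.2) + 12 × (1 − 0.4) = 8.0 + 7.2 = 15.2, against 15 required.
- Design effect: 1 + 0.12 × (15 − 1) = 2.68. Then 381 × 2.68 = 1021.08, rounded up to 1022; 1022 / 15 = 68.1, rounded up to 69 homes.
- Total: 69 × 44 = 3036, of whom 69 × 24 = 1656 are residents.

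All agree with Section 2.5, and the point disputes none of them.

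**Step 4. Size the group.**
- Expected resident drop-outs, applying 0.4 to all residents: 0.4 × 1656 = 662.4, about 662. Section 2.5 itself applies 0.4 to the 12 seronegative residents per home: 12 × 69 = 828, and 0.4 × 828 = 331.2, about 331.
- The Protocol gives no split by reason. With an assumed 10–30% non-death share: 0.10 × 662.4 = 66 and 0.30 × 662.4 = 199, or about 1 to 3 residents per home (66/69 = 1.0; 199/69 = 2.9).
- At an assumed 50%, the figure would be 0.50 × 662.4 = 331.

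These are counts of residents without a fitting code. They are not counts of missed deaths.

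**The case against.** The strongest reply is that a resident in hospital on the test day is still enrolled. The researcher completes the form from the head nurse or representative, so the resident need not be present and the opening question can be answered yes. Section 4.3 treats hospitalisation as a missing test result, and Section 2.7.3 has the reason documented. The form returns every two months, so a later death can still be entered with its date.

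Much of this stands. A reader might infer that hospitalised residents are coded as refusals and that their later deaths are lost. The documents do not support that: no section prescribes the coding, and none says that an absence closes the record. Nor do they support converting the gap into a percentage of deaths missed. The split of drop-out is unknown, some hospitalised residents would be only temporarily untested, and the recurring form can capture their deaths. A reader might also suppose that a resident who declines only the finger prick is treated as withdrawn. No section says so, and the consent text that would settle it is not in the copy reviewed.

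What the reply does not meet is the mismatch itself. Section 2.7.2 assigns hospitalisation as a drop-out reason to the questionnaire, and the resident form cannot hold it. The opening question merges still taking part with whether the form will be completed, so in the absence of a coding rule study centres may answer it differently. For transferred residents there is no code, no mention in Section 2.7.2 and no stated follow-up.

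**Conclusion.** The point holds as a contradiction within the Protocol: the resident form, in both languages, lacks codes for exits that Section 2.5 expects, one of which Section 2.7.2 says is collected. Such residents may be uncoded or mixed with undated refusals. The risk of missed deaths is firmest after transfer.

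The consequence is possible informative censoring in Section 3.2, item 6, and in item 9 if it is run. If residents who leave die more often than those who stay, the cause-specific hazards would be underestimated. The direction of any bias in the comparisons by serostatus or vaccination cannot be stated, because it depends on whether leaving differs between those groups, and the Protocol gives nothing on that.

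The 66–199 residents rest on two assumptions: that the 0.4 rate applies to all 1656 residents, and that 10–30% of drop-outs are non-death exits. Item 6 covers only fully vaccinated residents from 14 days after vaccination, so the number relevant there may be smaller. Seroprevalence, sero-incidence and the sample size arithmetic are untouched. The change is worth making because it is cheap and the missing data cannot be reconstructed afterwards.

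**What to change.** 1. In the Dutch and French resident follow-up forms, add three dated codes: temporarily absent or hospitalised (stays enrolled, may be tested on return); permanently transferred or left the home; other, with free text. Add a date to the refusal code.
2. In Section 2.7.2, add transfer to the list of reasons and state how the opening question is answered for an enrolled resident who is absent on the test day.
3. For residents who leave without withdrawing consent, have the clinical research coordinator ask the head nurse or representative at each later round for vital status, date and cause of death. Where this cannot be obtained, censor at the recorded exit date.

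The cost is a few fields in the online questionnaire and a line or two in Section 2.7.2, with a check that the consent wording covers vital-status enquiry after a move. The coordinator already approaches these informants each round. The downside is that vital status after transfer will remain incomplete for some residents, but they will at least be identifiable and dated.

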## QUESTIONNAIRE AU DÉBUT DE L'ÉTUDE

## Questionnaire sur les foyers de soins (à remplir au début de l'étude)

9. Numéro de référence de l'étude du centre d'hébergement
10. Quelle est la répartition en catégories de soins des résidents du centre d'hébergement (en chiffres absolus)?  
O:    A:    B:    C:    CD:    RÉ:
11. Une campagne de vaccination COVID a-t-elle déjà eu lieu au WZC?  
1er tour / 2ème tour (date)  
b. Quel vaccin?  
je. Vaccin AstraZeneca / Oxford  
ii. Le vaccin BioNtech-Pfizer  
iii. Le vaccin Moderna  
iv. Autres
2. Combien de résidents ont été vaccinés (par rapport au nombre total de résidents?)  
3. Combien d'employés ont été vaccinés (par rapport au nombre total d'employés?)
11. Votre hôpital a-t-il été touché par une ou plusieurs flambées de COVID-19 (= plusieurs infections au cours de la même période qui - vraisemblablement - peuvent être liées les unes aux autres) depuis le début de la crise jusqu'à maintenant?  
a. Au cours de quelle (s) période (s) le WZC a-t-il été affecté?  
b. Combien de membres du personnel et de résidents (environ) ont été testés positifs au cours de la même période?
12. Combien d'infections au COVID-19 suspectées ou confirmées y a-t-il eu dans le WZC parmi les résidents depuis le début de la crise jusqu'à aujourd'hui (environ) (y compris les résidents décédés)?
13. Combien d'infections au COVID-19 suspectées ou confirmées ont été commises au sein du WZC parmi les employés depuis le début de la crise jusqu'à maintenant (approximatif)
14. Combien de résidents sont morts du COVID-19 depuis le début de la crise jusqu'à maintenant (environ)?  
a. Décès confirmés au COVID-19  
b. Décès suspectés de COVID-19
15. Combien de résidents sont décédés de causes non liées au COVID depuis le début de la crise jusqu'à aujourd'hui (approximatif)

## Questionnaire individuel (à remplir au début de l'étude)

**Version pour les employés participants:**

10. Veuillez saisir votre numéro d'étudiant unique. (liste cfr avec nombres aléatoires et numéros d'étude, retournée par le centre de recherche UGent)

11. Veuillez entrer votre âge.

12. Quel est ton sexe? H / F

13. Quelle est votre position (activité principale) au sein du WZC

- Se soucier
- Administration
- Paramédical (kinésithérapeute, ergothérapeute, ...)
- Nettoyage
- cuisine
- Coiffeur / pédicure
- Autre (bénévole, animation, ...): (Remplissez l'option)

14. Travaillez-vous dans un service pour résidents atteints de démence? Oui Non

15. • Avez-vous été vacciné contre le COVID-19?

- Oui, une dose
- Oui, deux doses
- Non

o Si oui, quel vaccin vous a-t-il administré

☐ Le vaccin AstraZeneca / Oxford

☐ Le vaccin BioNtech-Pfizer

☐ Le vaccin Moderna

☐ autre

o Si oui, date de vaccination (première seringue).

16. Souffrez-vous de l'une des conditions suivantes? Indiquez ce qui s'applique (options de réponses multiples).

11. Maladie cardiaque et vasculaire

12. Diabète

13. Hypertension artérielle (hypertension)

14. Maladie pulmonaire / cardiaque / rénale sévère

15. Système immunitaire affaibli (troubles immunosuppresseurs) ou système immunitaire affaibli par l'utilisation à long terme de médicaments immunosuppresseurs (ex: chimiothérapie, patients transplantés, rhumatismes immunosuppresseurs, corticoïdes ...)

16. Maladie cancéreuse active

17. Aucune de ces réponses

17. Avez-vous été vacciné contre la grippe cette saison? (Cette question sera reflétée dans le questionnaire lors du dernier suivi)

18. Avez-vous déjà été testé pour le coronavirus (via PCR / test rapide AG / ou radiologique via CT scan)? Oui Non

19. Si oui, avez-vous déjà été testé positif pour le coronavirus? (Plusieurs options de réponse)

- Oui, via un test PCR (test dans lequel un échantillon est prélevé via un écouvillon nasal et vous obtenez le résultat après analyse en laboratoire)

- Oui, via un test rapide d'antigène (test dans lequel un échantillon est prélevé via un tampon nasal et le résultat peut être lu en 15 minutes)
  - Oui, radiologiquement, via un scanner
  - non
14. Si oui, date du 1er test PCR positif ou test rapide (approximative)?
15. Si le COVID-19 a été confirmé radiologiquement par un scanner, indiquez la date de ce scanner.
16. Si vous avez déjà été testé positif, quelle était la source probable de contamination?
- Au sein du WZC
  - En dehors du WZC
  - La source de la contamination m'était inconnue
17. Avez-vous ressenti un ou plusieurs des symptômes suivants pendant une période comprise entre février 2020 et maintenant, sans aucune explication claire à ce sujet? Indiquez ce qui s'applique (options de réponses multiples).
- Toux
  - Essoufflement
  - Douleur thoracique
  - Perte de goût
  - Perte d'odeur
  - Aggravation des maladies respiratoires chroniques (ex: BPCO, asthme, toux chronique, ...)
  - Fièvre
  - fatigue musculaire
  - Fatigue
  - Nez qui coule / bouché
  - Gorge irritée
  - Mal de crâne
  - Perte d'appétit
  - La diarrhée
  - Confusion aiguë
  - Chute soudaine
18. Si oui, quand avez-vous ressenti ces symptômes? Veuillez indiquer le jour approximatif où ces symptômes ont commencé.

